##### Data analysis

Frequency distributions, measures of central tendency, and variability will be calculated for all variables of interest. The outcomes and maternal and infant conditions (e.g., maternal depression, weight, height, infant age, type of feeding) will be compared across groups at baseline using multivariate analysis of variance (MANOVA), chi-square tests, or Generalized Linear Mixed Effects Models (GLME) with Poisson or gamma distributed errors, if normalizing transformations are not successful for continuous variables. If differences between groups are observed despite computerized minimization, the relevant variables will be treated as covariates in our post-experiment analyses. The primary analysis is of the intent-to-treat type.

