### Participants and recruitment

Participants with the following characteristics are being recruited: low-income (≤ 185% federal poverty level in the US and eligible for federal food assistance programs); 18 years of age or over; mothers of infants less than 4 months of age who have not started solid foods; a primary caregiver of the infant, and neither mother nor infant has a diagnosed eating, physical, or chronic health problem. Mother-infant dyads are targeted for recruitment from local community programs, such as the Special Food Supplemental Nutrition Program for Women, Infants, and Children (WIC), a federal assistance program of the Food and Nutrition Service of the USDA, food pantries, hospitals, physicians' offices, and immunization clinics. Staff from these programs provide information about the study and encourage mothers with infants to enroll in the project.

Once eligibility is established, families are contacted for the initial data collection home visit where written informed consent is obtained. Newly recruited participants are not previously enrolled in EFNEP. We have obtained ethical approval to conduct this trial from the University Committee on Research Involving Human Subjects from Michigan State University and the Institutional Review Board for Human Subjects from Colorado State University. Informed consent for voluntary participation is obtained prior to commencement in the study.

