### Randomization

Following consent and baseline data collection, mothers are randomized into either the HB or control group. This is done via computer minimization procedure, balancing groups with respect to the county recruitment locations. According to CONSORT guidelines [13], allocation concealment is used to prevent participants, data collectors, and paraprofessionals from knowing which group the participants will be assigned. Only after enrollment in the program do researchers assign participants into intervention or control groups. The assignment of groups is withheld from data collectors throughout the entire length of the study. Separate paraprofessional instructors deliver either the HB intervention or the traditional nutrition education; separate individuals who are not paraprofessional instructors are trained as data collectors in each county to do the in-home data collection at each time period.

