### Maternal and infant conditions that may influence outcomes

Maternal depression and infant temperament are conditions that may impact the effectiveness of the intervention. Maternal and infant conditions will be assessed at the three time points. Maternal depression data will be collected using three questions from the Edinburgh Postnatal Depression Scale (EPDS-3) [18], which has an internal consistency of .8 [18]. Infant temperament will be assessed using the Revised Infant Behavior Questionnaire (IBQ-R) [19], a 47-item measure with internal reliability range of .73-.94. At baseline, we will also collect data on the mother's age, education, history of infant feeding, work status and occupation, ethnicity, marital status, number of adults in the home, and the presence of other adult caregivers (e.g., grandmother).

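### Choosing covariates by observed baseline differences catches only chance imbalance and gives up precision; planned power is kept and the overall type I error turns conservative

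*Protocol article*

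**What the plan says.** The Data analysis section begins by comparing the arms at baseline. The variables compared are "The outcomes and maternal and infant conditions (e.g., maternal depression, weight, height, infant age, type of feeding", and these "will be compared across groups at baseline using multivariate analysis of variance (MANOVA), chi-square tests" or generalised linear mixed models. The rule follows: "If differences between groups are observed despite computerized minimization, the relevant variables will be treated as covariates in our post-experiment analyses". No threshold for a difference is given. The next sentence states that the primary analysis is by intention to treat.

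Two statements under Randomization bear on this. On timing: "Following consent and baseline data collection, mothers are randomized into either the HB or control group". On the allocation method: "This is done via computer minimization procedure, balancing groups with respect to the county recruitment locations". No other balancing factor is listed.

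A separate section on maternal and infant conditions says: "Maternal depression and infant temperament are conditions that may impact the effectiveness of the intervention". Under the rule, these conditions too would enter a model through an observed imbalance.

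Sample size and power calculations gives a minimal detectable effect of d = .33 (80% power, two-sided 5%), a reported effect of d = .35, and 139 dyads per group for analysis. It also mentions a model with a group-by-time interaction over two time points, without saying which two.

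**The concern.** Baseline data precede allocation, so, if allocation is sound, the null hypothesis of each baseline comparison is true by design. A significant result is then a chance event. The usefulness of a covariate depends on how strongly it predicts the outcome, and a baseline comparison between arms carries no information about that. A strongly prognostic variable that looks balanced would be left out, and a useless one that looks imbalanced would be put in.

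The reference to minimisation gives little comfort for most of the screened variables. Minimisation works on county, and depression, weight, infant age and feeding type are not among its factors.

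Two things are at stake. The form of the outcome models is not settled until the baseline comparison has been made, with no stated threshold for making it. And the precision that fixed adjustment would give is mostly forgone.

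This is not a detail that a condensed article may leave to the analysis plan. The article states a selection rule, and a later plan could repair it only by departing from this text.

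**Working it through.** **1. The plan's own figures.** Inputs from Sample size and power calculations: 139 per group, two-sided 5%, 80% power, d = .33, 25% attrition.

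- Minimal detectable effect = (1.960 + 0.842) × √(2/139) = 0.336, against the stated .33.
- Power at d = .33 with 139 per group is 78.6% by the normal approximation. The gap from 80% is rounding.
- Enrolment: 139 / 0.75 = 185.3, rounded up to 186 per group, 372 in total, as stated.

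These figures use no covariates. The plan's power therefore does not rely on adjustment.

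**2. How often the rule admits a covariate.** With an assumed 5% cut-off, a variable measured before allocation is flagged in about 5% of trials, however prognostic it is. In about 95% of trials it is left out.

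**3. What that costs.** Simulation with 139 per group, d = .35, and one normally distributed baseline covariate with correlation ρ to the outcome. The rule is ANCOVA if the baseline t-test has p < .05, otherwise an unadjusted t-test. Fixed adjustment is ANCOVA in every trial. The article gives neither ρ nor the cut-off, so both are assumptions and a range of ρ is shown.

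| ρ | Power, rule | Power, fixed ANCOVA | Type I error, rule |
|---|---|---|---|
| 0 | about 83% | about 83% | about 5% |
| .3 | about 83% | about 86% | about 4.8% |
| .5 | about 84% | about 92% | about 4.2% |
| .7 | about 85% | about 98% | about 3.6% |

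Fixed ANCOVA keeps its type I error at about 5% throughout.

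**4. Check by formula.** Power = Φ(d × √(n/2) / √(1 − ρ²) − 1.960), with d × √(n/2) = .35 × √69.5 = 2.918.

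- ρ = 0: Φ(0.958) = 83.1%
- ρ = .3: Φ(2.918/0.954 − 1.960) = 86.4%
- ρ = .5: Φ(2.918/0.866 − 1.960) = 92.1%
- ρ = .7: Φ(2.918/0.714 − 1.960) = 98.3%

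**5. At the plan's own d = .33.** Rule against fixed ANCOVA: 78.6% vs 81.8% (ρ = .3), 79.6% vs 88.5% (ρ = .5), 80.2% vs 96.9% (ρ = .7). The gain forgone is about 3, 9 and 17 points.

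**The case against.** **The harm is limited.** A reader might infer that the rule inflates false positives or leaves the trial underpowered. The documents support neither. The type I error moves down on average, and the trial is sized without covariates, so its planned power of about 80% stands. This objection holds and sets the severity. One qualification: the average hides a conditional weakness. In simulated null trials where the baseline difference is moderate but misses the cut-off (|t| from 1.2 to 1.97), the unadjusted test rejects in roughly 6.5%, 8% and 11% of cases at ρ = .3, .5 and .7. That does not raise the overall rate.

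**The sizes rest on assumptions.** The correlation and the cut-off are not in the article, and nothing in it supports a floor of .3 for measures taken before 4 months of age against those at 6 or 12 months. At d = .35 the gain from fixed adjustment is 0.4 points at ρ = .1 and 1.5 points at ρ = .2. This stands. Nor can one say how many variables would be flagged by chance: the number of tests is not given, and MANOVA is a joint test.

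**The model may already use the baseline outcome.** If baseline is one of the two time points in the group-by-time model, the comparison above does not apply to the baseline outcome itself. A change-type contrast at d = .35 has standard deviation √(2(1 − ρ)), giving Φ(2.918/0.775 − 1.960) = 96.5% at ρ = .7, close to ANCOVA. At ρ = .3 it gives Φ(2.918/1.183 − 1.960) = 69.4%, below even the unadjusted test. So the loss would differ in either direction, and it would remain for other prognostic variables. It would go too far to say that the plan certainly discards the baseline outcome.

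**The rule does not say that only differing variables enter.** True; exclusion of the others is the natural reading, not an explicit statement. Likewise, the article does not show that infant age at baseline strongly predicts outcomes measured at fixed ages, so it is only a candidate covariate.

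**Conclusion.** The concern holds at moderate severity. The article fixes a covariate rule driven by chance imbalance. With one covariate, a 5% cut-off, 139 per group, d = .35 and no other use of the baseline outcome, the rule forgoes about 3, 8 and 13 points of power at ρ = .3, .5 and .7 (86 − 83, 92 − 84, 98 − 85), and nothing at ρ = 0. Type I error is about 4.8%, 4.2% and 3.6% instead of 5%. These figures show what is available under stated assumptions and do not estimate this trial's actual loss. The planned unadjusted power is intact, and the trial's validity is not in question.

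**What to change.** Replace the sentence on observed differences with a rule set before outcome data are seen:

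- Each outcome model adjusts for the baseline value of that outcome, for county (the minimisation factor), and for a short pre-named list of prognostic variables already collected, for example infant age at baseline, whatever the observed balance.
- For solid-food items, use baseline feeding type. Eligibility is limited to "mothers of infants less than 4 months of age who have not started solid foods", so these items are zero at baseline and carry no information.
- Report baseline characteristics descriptively by arm, without significance tests.
- Label any further adjustment for a chance imbalance as a sensitivity analysis.
- State which two time points the group-by-time model covers, so that it is clear whether the baseline outcome is a response or a covariate.

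The cost is one paragraph in the protocol or analysis plan. The variables named are already collected, and neither the sample size nor the visit schedule changes.

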## Discussion

If this project is successful, the expected outcomes are that the intervention will be effective in helping mothers with young infants develop healthy infant feeding practices that will contribute to the overall health and development of the infant, and in reducing the risk of childhood obesity in vulnerable populations. If effective, the Healthy Babies project will result in a targeted baby-centered feeding support-education intervention targeting economically and educationally disadvantaged mothers of infants under the age of 1 year. Very few empirical studies have focused on early feeding interventions, yet many new parents, particularly lower-income parents, lack key knowledge about basic infant nutrition and feeding needs.

Our home visitation model refers to a structured model of interaction with families over a period of time. This type of home visitation is implemented as a primary prevention strategy. Cost-effectiveness of the HB intervention program will be considered in terms of intensity of services (e.g., number of visits) and qualifications and salary requirements of staff. One limitation to the study, however, is the use of convenience sampling, which may limit the generalizablity of the study findings to the target population. The "product" will be an intervention that can be used within community settings and is accessible, feasible, and accepted by the target population. The long-term goal of this intervention is to contribute to curbing the rising rates of childhood obesity through an effective multi-component, relationship skill-building, educational intervention that fosters infant-centered feeding to promote healthy maternal responsiveness, feeding styles, and feeding practices as infants transition to solid foods.

## List of Abbreviations

HB: Healthy Babies; RCT: randomized controlled trial; TPB: theory of planned behavior; USDA: United States Department of Agriculture; EFNEP: Expanded Food and Nutrition Education Program; WIC: Women, Infants and Children; NCAST: Nursing Child Assessment Satellite Training; MDES: minimal detectable effect size; PCI-F: Parent-Child Interaction Scale-Feeding; NCAFS: Nursing Child Assessment Feeding Scale; IFSQ: Infant Feeding Styles Questionnaire; TIFS: The Infant Feeding Scale; EPDS: Edinburgh Postnatal Depression Scale; IBQ-R: Revised Infant Behavior Questionnaire; PM: project manager; MANOVA: multivariate analysis of variance; GLME: Generalized Linear Mixed Effects Model; HBICF: Healthy Babies Infant-Centered Feeding.
